## 15.0 RESEARCH PARTICIPANT REGISTRATION AND RANDOMIZATION PROCEDURES

### 15.1 Research Participant Registration

#### MSKCC only

Confirm eligibility as defined in the section entitled Criteria for Patient/Subject Eligibility.

Obtain informed consent, by following procedures defined in section entitled Informed Consent Procedures.

During the registration process registering individuals will be required to complete a protocol specific Eligibility Checklist. The individual signing the Eligibility Checklist is confirming whether or not the participant is eligible to enroll in the study. Study staff are responsible for ensuring that all institutional requirements necessary to enroll a participant to the study have been completed. See related Clinical Research Policy and Procedure #401 (Protocol Participant Registration).

#### 15.1.1 For Participating Sites:

Central registration for this study will take place at MSKCC.

To complete registration and enroll a participant from another institution, the study staff at that site must contact the designated research staff at MSKCC to notify him/her of the participant registration. The site staff then needs to fax registration/eligibility documents to the Department of Surgery at MSKCC: [contact], Attn: MSKCC Study Coordinator. If scanned copies are sent, they must be sent using secured or password-protected e-mail. Scanned copies can be e-mailed to the MSKCC Study Coordinator [[contact]](mailto:[contact]). Faxed submissions should include a cover page listing all documents included per participant.

The following documents must be sent for each enrollment within 24 hours of the informed consent form being signed:

- The completed or partially completed MSKCC Eligibility Checklist
- The signed Informed Consent and HIPAA Authorization form
- Supporting source documentation for eligibility questions (laboratory results, pathology report, radiology reports, endoscopic reports, MD notes, physical exam sheets, medical history, prior treatment records, and EKG report).

Upon receipt, the research staff at Memorial Sloan Kettering Cancer Center will conduct an interim review of all documents and will associate the participant to the study in MSK's Clinical Trials Management System (CTMS). The participant will be assigned a protocol participant number in CTMS. This number will be relayed back to the study staff at the registering participating site via e-mail and will serve as enrollment confirmation. The number is unique and must be written on all data and correspondence for the participant.

If the eligibility checklist is not complete or source documentation is missing, the participating site will be responsible for sending the completed registration documents within 30 days of the consent. Once the external registration submission is complete, if the participating site IRB has granted approval for the protocol and the participating site is in good standing, the MSK study coordinator will fully register the participant in CTMS. The participating site will be notified by the MSK study coordinator when registration is complete.

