## **6.0 CRITERIA FOR SUBJECT ELIGIBILITY**

### **6.1 Subject Inclusion Criteria**

- Histologically confirmed diagnosis of adenocarcinoma of the rectum.
- Clinical Stage II (T3-4, N-) or Stage III (any T, N+) based on MRI
- Rectal tumor at baseline which would be considered to require complete TME
- No evidence of distant metastases
- No prior pelvic radiation therapy
- No prior chemotherapy or surgery for rectal cancer
- Age  $\geq$  18 years. The minimum legal age of consent for select Canadian provinces is 19
- No active infections requiring systemic antibiotic treatment (oral antibiotics are acceptable at the discretion of the treating physician)
- ECOG Performance status 0-2
- Women with childbearing potential (WOCBP) who are negative for pregnancy test (urine or blood) and who agree to use effective contraceptive method. A woman of childbearing potential is defined as one who is biologically capable of becoming pregnant. Reliable contraception should be used from trial screening and must be continued throughout the study.
- Patients must read, agree to, and sign a statement of Informed Consent prior to participation in this study. Patients who do not read or understand English are eligible and may be consented according to institutional and federal regulations.
- ANC > 1.5 cells/mm^3, HGB > 8.0 gm/dl, PLT > 150,000/mm^3, total bilirubin  $\leq$  1.5 x ULN (except in patients with Gilbert's Syndrome who must have total bilirubin  $\leq$  3.0 x ULN), AST  $\leq$  3 x ULN, ALT  $\leq$  3 x ULN.

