#### **9.5. MRI**

All MRIs must meet the following minimum requirements. Appendix F lists in detail the technical and quality requirements for MRI Scans.

- 1.5 or 3.0 Tesla machine
- Use of phased array coil
- T2-Weighted axial, sagittal, and coronal images small field of view: 14-24 cm
- T2-Weighted axial and sagittal images maximum slice thickness: 3-4mm (5mm slice will not be accepted)
- T2-Weighted images should not be fat saturated
- Large field of view axial T1 and T2 from aortic bifurcation to inguinal region slice thickness: 5-7mm accepted

Baseline MRI images will be collected for the first two patients enrolled at each participating site to assess image quality. Baseline MRI images should be submitted to the MSKCC Study Coordinator within 5 business days of patient consent. If the MRI does not meet quality standards, feedback will be returned to the site with 48 hours. Quality and central imaging review will be performed at MSK. For detailed technical and quality requirements for MRI scans, please see Appendix F.

At baseline only, MRIs may be performed at a local imaging center external to a participating site, however they must be reviewed by the site radiologist and submitted to MSK for central review and approval. Disks should be submitted at least two weeks prior to treatment start, or

to allow enough time to re-scan the patient prior to treatment start, if necessary. This is in the event that outside MRIs do not follow the MRI requirements outlined in Appendix F.

MRI images taken at interval evaluation are required for all MSK patients and recommended for participating sites. For all patients with images taken at the interval and re-staging evaluations we are asking sites to submit these images to MSK for central review. For radiologic exams done during the interval and restaging evaluations, images should be submitted within 5 business days of the date of review by the participating site radiologist. These images should be de-identified, labeled with the unique study number, and submitted to the MSKCC Study Coordinator on disks in DICOM format. Submitted MRI reports should indicate staging and if nodes are positive or negative. N staging of N- or N+ are accepted. If the MRI does not meet the technical and clinical standards outlined in Appendix F, feedback will be returned to the site within 24 hours. Local and central interpretation will be tracked.

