## **15.2 Randomization**

This is a randomized phase II study with Arm 1 receiving INCT prior to CRT while Arm 2 receives CRT followed by CNCT. After eligibility is established and after consent is obtained, patients will be registered in the Protocol Participant Registration (PPR) system, and randomized using the Clinical Research Database (CRDBi-Multicenter). If a patient is pending registration based on limited available information, randomization will occur after all completed documentations is received. A patient may be registered as pending for up to 30 days from the initial registration submission to PPR. Randomization will be stratified per institution and accomplished by the method of random permuted block. Since this is not a blinded study, all study investigators may view randomization in the CRDBi-Multicenter.

For participating institutions other than MSKCC, randomization will be stratified per institution and determined using the same method for MSKCC patients as noted above. Confirmation of the treatment plan for randomized participants will be sent by the MSKCC research staff via e-mail, along with the participant ID, to the study coordinator and the site Principal Investigator within 48 business hours of receiving all completed required enrollment documents.

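### Central approval of an outside baseline MRI is not a condition of randomization, so a staging scan can be rejected and repeated after the open-label arm is known

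*Protocol*

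**What the plan says.** MRI stage decides eligibility. Protocol 6.1 admits "Clinical Stage II (T3-4, N-) or Stage III (any T, N+) based on MRI". Section 8.2 allows the baseline MRI to be done at an outside institution. For scans from an imaging center external to a participating site, 9.5 says "they must be reviewed by the site radiologist and submitted to MSK for central review and approval". On timing, 9.5 says "Disks should be submitted at least two weeks prior to treatment start", or early enough "to allow enough time to re-scan the patient prior to treatment start, if necessary". The reason it gives for a re-scan is failure to meet the technical requirements of Appendix F.

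Registration of patients from participating sites is governed by 15.1.1: "The following documents must be sent for each enrollment within 24 hours of the informed consent form being signed". The list that follows includes "Supporting source documentation for eligibility questions (laboratory results, pathology report, radiology reports, endoscopic reports" and further clinical records. Images and central MRI approval are not on it. An incomplete packet may be completed within 30 days of consent.

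Section 15.2 places randomization after eligibility and consent. A patient with missing documents is held as pending for up to 30 days. The treatment assignment goes to the site "within 48 business hours of receiving all completed required enrollment documents". The trial is not blinded, and investigators may view the allocation in the database.

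**The concern.** Central approval is mandatory for an outside scan, yet it is tied to treatment start and not to randomization. A site that follows every stated step can register the patient on the report, learn the arm, and only then hear that the scan was not acceptable. The repeat scan is read locally by staff who may know the arm.

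If the repeat puts the patient outside stage II or III, section 13 says that a patient found ineligible after enrollment is removed from the study. That conflicts with the statements in 1.0 and 4.1 that all patients are followed by intent-to-treat. It also conflicts with the opening of section 13, which names withdrawal of consent as the only ground for removal. Removals decided with the arm known can differ between arms, and randomization no longer protects against that.

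**Working it through.** No sample-size or power figure is involved. The check is the order of the stated steps, then their deadlines, then the possible size.

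**Order of steps**

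| Step | Section | Tied to |
|---|---|---|
| Local MRI reading for eligibility | 9.3.4.2, 9.5 | Treating center |
| Packet with radiology reports | 15.1.1 | 24 hours after consent |
| Randomization and arm notice | 15.2 | Complete packet |
| Disk of an outside MRI, any re-scan | 9.5 | Treatment start |
| Coordinator's eligibility check | 16.0 | Treatment start |

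The last two rows have no limit relative to randomization, and no section links central approval to registration or allocation. The gap in sequence follows from this alone.

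**Deadlines**

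Take consent as day 0 and count business days.

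- The packet is due on day 1 (24 hours).
- The arm notice follows within 48 business hours, a term the protocol does not define. At 24 hours per business day it adds 48/24 = 2, giving day 1 + 2 = 3. At 8 hours per business day it adds 48/8 = 6, giving day 1 + 6 = 7. Both conversions are assumptions.
- The image verdict depends on which deadline applies. Sections 9.3.4.2 and 9.5 allow 5 business days for baseline images, and 9.5 gives 48 hours for quality feedback. Taking that as two days gives 5 + 2 = 7. The 16.0.2 schedule gives 24 hours for baseline source documents, and 16.0.1 counts baseline MRI images among these, which gives 1 + 2 = 3. However, 16.0.1 refers back to 9.3.4.2, and 16.0.2 refers to 15.1.1, so the deadlines do not agree.

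Verdict minus arm notice:

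| | Arm notice day 3 | Arm notice day 7 |
|---|---|---|
| Verdict day 7 | 7 − 3 = +4 | 7 − 7 = 0 |
| Verdict day 3 | 3 − 3 = 0 | 3 − 7 = −4 |

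The difference runs from −4 to +4 business days, and every entry is built from latest dates. The 48-hour feedback is also stated with the quality check of the first two patients per site. The paragraph on outside scans gives no feedback time.

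**Size**

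- Section 7.0 plans 238 of 325 patients at participating sites: 238/325 = 73%.
- The share with an outside scan is not given, so the number of such scans lies between 0 and 238.
- As an illustration only, assume that 10–30% have an outside scan and 5–15% of those are rejected. Low end: 238 × 0.10 × 0.05 = 1.2. High end: 238 × 0.30 × 0.15 = 10.7. That is about 1 to 11 re-scans, or 1.2/325 = 0.4% to 10.7/325 = 3.3% of accrual.
- These are re-scans. Patients who become ineligible are an unknown fraction of them.

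**The case against.** The strongest reply is that 15.2 already puts randomization after eligibility has been established, and MRI stage is an eligibility criterion. Section 9.3.4.2 gives the eligibility reading to the treating center, and 9.5 requires the site radiologist to review an outside scan. On this reading eligibility is settled locally before randomization, and the central step is a check of image quality. Much of this stands: rejection is for technical non-conformity, a repeat need not change the stage, and no section says that a rejected scan voids eligibility. But 15.2 does not name central approval, and 9.5 calls for approval as well as review. A scan below the required standard was the basis of the staging, so its replacement can change the stage.

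A second reply is that images are in fact requested at baseline, in 16.0.1 and 16.0.2. That is correct. It leaves conflicting deadlines, and asking for images does not make their approval a condition of randomization.

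Two stronger readings are tempting. A reader might infer that the arm is always known about four business days before the MRI verdict. That holds for only one combination of undefined terms and conflicting deadlines. A reader might also infer that eligibility is routinely re-decided by allocation, or that up to 11 patients become ineligible after randomization. The documents give no rate of outside scans, rejections or stage changes, and the 11 is an assumed count of re-scans.

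**Conclusion.** The sequencing gap is real and minor. For outside baseline MRIs, the protocol permits randomization before an approval that it requires, and it sends a patient later found ineligible out of the study. This rests on the text of 9.5, 13, 15.1.1 and 15.2 and on no assumed rate.

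The number affected is unknown and probably small. Section 14.1 tests each arm against a historical rate and plans no formal comparison of the arms on DFS. The exposure is therefore mainly in the secondary arm comparisons and in the 14.2 pick-the-winner rule, which turns on a difference of 5 NOM patients. The documents do not show that removals by this route would reach that margin or differ by arm.

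**What to change.** 1. In 15.1.1 and 15.2, state that where the baseline MRI was done outside the site, central approval under 9.5, including any re-scan, must be on file before full registration and randomization. Until then the patient stays in the existing pending status, up to 30 days.
2. In 9.5, state that disks of outside scans must be sent in time for approval or re-scan before randomization. Treatment start is mentioned twice in that sentence. A word-for-word substitution would turn the two-week lead into a two-week wait before randomization, so the sentence should be rewritten without carrying that lead over.
3. Reconcile the baseline image deadlines: 24 hours in 16.0.2 against 5 business days in 9.3.4.2 and 9.5.

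The cost is a few lines of wording and a delay in randomizing these patients while the images are reviewed. No sample size or endpoint changes. According to 14.1 the original accrual is already complete, so the edit protects only patients randomized later. It also does not settle the conflict between section 13 and the intent-to-treat statements for patients found ineligible on other grounds.

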## **15.2 Randomization**

This is a randomized phase II study with Arm 1 receiving INCT prior to CRT while Arm 2 receives CRT followed by CNCT. After eligibility is established and after consent is obtained, patients will be registered in the Protocol Participant Registration (PPR) system, and randomized using the Clinical Research Database (CRDBi-Multicenter). If a patient is pending registration based on limited available information, randomization will occur after all completed documentations is received. A patient may be registered as pending for up to 30 days from the initial registration submission to PPR. Randomization will be stratified per institution and accomplished by the method of random permuted block. Since this is not a blinded study, all study investigators may view randomization in the CRDBi-Multicenter.

For participating institutions other than MSKCC, randomization will be stratified per institution and determined using the same method for MSKCC patients as noted above. Confirmation of the treatment plan for randomized participants will be sent by the MSKCC research staff via e-mail, along with the participant ID, to the study coordinator and the site Principal Investigator within 48 business hours of receiving all completed required enrollment documents.

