Based on previous data, we anticipate a 20% NOM in the INCT arm, and 35% in the CNCT arm, after 3 years. The proportion of patients initially entered in the NOM protocol will be higher, but some will later relapse and require TME. For this reason, we anticipate that the proportion of patients with NOM at 3 years will be close to the pCR rates observed in previous studies. We estimated that the 222 patients required for the primary aim would be sufficient to detect differences in organ preservation rates. Our preliminary results indicate that the proportions of patients selected for NOM based on tumor response after completion of neoadjuvant therapy are much greater than expected: 66% in one arm and 79% in the other. Although many of these patients may eventually experience tumor regrowth requiring total mesorectal excision, the proportions of patients with a preserved rectum 3 years after diagnosis are likely to be greater than the original estimates. Therefore, based on the new information, we plan to increase accrual to 325 patients. There is limited information regarding treatment compliance and adverse events in patients who have received more than 4 or 6 cycles of INCT or CTNT. Therefore, these secondary objectives are considered exploratory. If both arms meet the endpoint in primary objective, we plan to use NOM rate to determine the more promising regimen using a “pick the winner” strategy. We will calculate the number of patients treated with NOM who are alive and free of disease 3 years following the start of the study. We will require at least 20 NOM patients in each arm to employ the following strategy: If there is a difference of 5 NOM patients between arms, the arm with more NOM patients will be deemed the winner. With 101 patients in each arm, 20% NOM in patients treated with INCT and 30% in patients treated with CNCT, we will have an 83% probability of selecting CNCT, a 1% probability of selecting INCT, and a 16% probability of considering the study inconclusive.

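### Open viewing of allocations, site-level permuted blocks and a pending window that the site can end together weaken allocation concealment

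*Protocol*

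**What the plan says.** Protocol section 15.2 sets the method: "Randomization will be stratified per institution and accomplished by the method of random permuted block". Outside centres use the same method. Institution is the only stratification factor named. On access, the section states: "Since this is not a blinded study, all study investigators may view randomization in the CRDBi-Multicenter". The lack of blinding is the only reason given. The section does not say whether the view covers all sites or only the investigator's own.

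On timing, section 15.2 says: "If a patient is pending registration based on limited available information, randomization will occur after all completed documentations is received", and "A patient may be registered as pending for up to 30 days from the initial registration submission to PPR". Section 15.1.1 allows a partly completed eligibility checklist at first submission and adds that "the participating site will be responsible for sending the completed registration documents within 30 days of the consent". It also contains a safeguard: registration is central, and the first set of documents is due within 24 hours of signed consent.

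Section 14.2 contains the decision that depends most directly on comparable arms: "If there is a difference of 5 NOM patients between arms, the arm with more NOM patients will be deemed the winner". It applies only if both arms meet the primary endpoint and each has at least 20 NOM patients. Nothing in the protocol restricts who sees the allocation history or requires pending patients to be randomised in order of registration.

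**The concern.** Open treatment does not require an open allocation record. Blinding concerns what is known after assignment; concealment concerns what can be guessed before it. Within a site, permuted blocks pull the running count back towards balance, so whoever sees that count can guess the next arm better than chance. Usually the guess is of little use, because a consented patient takes the next slot at once. Here the slot is taken when the site sends its last document, at any time within the window, so two pending patients can be entered in either order. The reordering need not be deliberate.

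At stake are the comparisons of organ preservation, compliance and adverse events, and the choice of a winning regimen on a margin of 5 patients. Sections 14.1 and 14.2 raise accrual from 222 to 325 because of the organ-preservation comparison, so the added patients serve the analysis that concealment protects.

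**Working it through.** **1. The plan's own figure.** For the winner rule, section 14.2 gives 83% (CNCT), 1% (INCT) and 16% (inconclusive), with 101 per arm and NOM rates of 20% and 30%. The exact difference of two binomials, with a win at 5 or more, gives 82.0%, 0.9% and 17.1%. This agrees within 2 points, without applying the 20-patient condition. The protocol gives no figure for how predictable the allocation is.

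**2. Guessing the next arm.** Block size is not stated, so a range is assumed (1:1 allocation). The rule is to guess the arm that is behind, or toss a coin when level. It needs no knowledge of block size.

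| Block size | Correct guesses | Known with certainty, only if the size is fixed and known |
|---|---|---|
| 2 | 75% | 50% |
| 4 | 71% | 33% |
| 6 | 68% | 25% |
| 8 | 67% | 20% |
| 4 and 6 mixed | 69% | not applicable |
| 2, 4 and 6 mixed | 70% | not applicable |

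**3. What the view adds.** Simulation with 24 patients per site, spread at random over 3 to 6 investigators (both assumed), and blocks of 4 or 6, fixed or mixed: an investigator who sees the whole site history is right about 70% of the time. One who sees only their own patients is right about 52 to 54% of the time.

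**4. Room to use the guess.** Section 7.0 expects 87 patients at MSKCC and 238 elsewhere; section 14.1 gives 40 months. With Poisson arrivals and a 30-day month:
- MSKCC: 87/40 = 2.175 per month; chance of at least one other randomisation in the window = 1 − exp(−2.175) = 89%.
- Outside centres: 238/40 = 5.95 per month in all. With 10 equal centres (assumed), 1 − exp(−0.595) = 45%; with 20, 1 − exp(−0.2975) = 26%.

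**5. Possible bias.** Let p be the correct-guess rate. Let D be the difference in 3-year NOM success between patients entered when one arm is expected and those entered when the other is. The bias in the arm difference is D × (p − (1 − p)) = D × (2p − 1). D is not in the documents; 5 to 10 points is assumed. For blocks of 4, 2p − 1 = 0.417, so the bias is 2.1 to 4.2 points, or 3.4 to 6.8 patients per 162.

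With 162 per arm, 50% NOM in both (assumed) and no true difference, each arm reaches the 5-patient margin 31% of the time. With that bias, the favoured arm wins 45% (D = 5) or 60% (D = 10). This is an upper bound, since it lets every patient's entry be timed.

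**6. What can still be changed.** If only the added patients remain, 325 − 222 = 103, or 32%. Full exposure among them alone gives 0.7 to 1.3 points, or 1.1 to 2.1 patients per 162, and the favoured arm wins 35 to 40%.

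**The case against.** The strongest reply is that the view does little work. Only a site's own past allocations inform its next one, and section 15.2 already sends each assignment to the site's principal investigator and study coordinator. That stands for those two roles, and restricting the view leaves their knowledge unchanged. It does not stand for the other investigators at a site with several, as step 3 shows. Because the site's staff also send the documents, the order rule is needed as well.

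Other objections stand in part:
- Varying the block size barely helps: p = 0.69 gives 2p − 1 = 0.38, against 0.417 for blocks of 4.
- Pending status is meant only for incomplete documents, and notice within 24 hours makes a dropped or reordered patient traceable. It does not prevent delay or reordering.
- The room for timing is smaller at low-accruing centres.
- D is an assumption, and nothing in the protocol shows that sites favour an arm.
- Compliance and adverse events are labelled exploratory, and the winner rule is conditional.

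A reader might infer that sites can know the next arm, or that the missing block size is itself a fault. The document supports neither. Block size is rightly kept out of a protocol, and certainty requires it to be both fixed and known. Nor does the text say that upcoming assignments are shown. That the view reveals past allocations is the natural reading of the sentence, not its literal wording.

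**Conclusion.** The point holds as a weakness in concealment, created by what sections 15.1.1 and 15.2 positively state. With the site's history in view, the next arm can be guessed 67 to 75% of the time for assumed blocks of 2 to 8, against 50% by chance, and the pending window gives the site some control over entry.

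The exposure is mainly in the between-arm secondary comparisons and the winner rule. If all entries could be timed, an assumed D of 5 to 10 points would give a bias of 3.4 to 6.8 patients per 162, against a margin of 5. For the 103 added patients alone it would be 1.1 to 2.1. These figures show what could happen; they do not estimate what has happened.

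A reader might also infer that the primary analysis is compromised. Section 14.1 tests each arm against a fixed 75% and plans no formal comparison of arms. If the same D applied to DFS, each arm would move by half the bias in step 5, about 1.0 to 2.1 points in opposite directions even at full exposure. The gap between 75% and the stated critical value of 82% is 7 points.

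**What to change.** Make two changes, both for patients still to be randomised.

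1. In section 15.2, replace the open-view sentence with wording such as: an investigator sees only their own patient's allocation, after that patient has been irrevocably randomised; the allocation history and list are restricted to central staff who do not enrol patients. The last clause matters because MSKCC is both the registration centre and an enrolling site.
2. In sections 15.1.1 and 15.2, state that pending patients at a site are by default randomised in order of registration. A later patient whose documents are complete may go first, with the reason logged, so that no fully documented patient is held back. The existing 24-hour notice supplies the order.

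Undisclosed, randomly varying block sizes are optional: they remove certainty but hardly lower the guess rate.

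The cost is a change of user permissions, a few sentences and a short log. Investigators lose the view across patients. The site's principal investigator and coordinator will still know their own site's assignments, so some predictability remains; the order rule limits its use, and the log makes exceptions visible.
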